#### Graded Motor Imagery (GMI) training

A graded motor cortical retraining program based on previous work by Wand et al. [13] and published guidelines [28] will be implemented.

The initial stage (weeks 1–2) of the GMI will involve laterality recognition training (Implicit Motor Imagery). An online computer program (Recognise Online, NOI Group, Adelaide, SA, Australia) will be used to present participants with a random selection of photographs of either their left or right shoulders [28]. The photographs will be presented in a variety of positions and orientations. Participants will respond by pressing one of two keys to indicate whether a picture shows the left or right shoulder, a process that require them to mentally rotate their own body part to match the position shown in the picture and, thereby, to engage motor cortical areas corresponding to that body part. An important aspect of the test is that it is performed unconsciously (relatively) so it should be done as quickly as possible, almost as though the patient was guessing [28]. The photographs will be presented in groups of 30 for a duration of 5 s for each photograph, and progression will involve reducing the time for which the photographs are presented and changing the background of the photographs. During an initial familiarization session conducted during the first formal treatment, three lots of 30 photographs will be presented with a 1-min rest period between lots. Participants will be asked to practice this task at home for 15 min each day.

The next stage (weeks 3–4) will involve imagined movements (Explicit Motor Imagery). Two videos, each lasting approximately 7 min will be made of a person slowly performing a variety of shoulder movements from simple, low-load movements to more complex, behaviourally relevant movements. During the first week of this stage (week 3), the video will show small-range shoulder movements (e.g., unilateral shoulder flexion, extension, abduction, shoulder external and internal rotation in 0° of abduction). In the second week of this stage (week 4), the video will show a person performing the same movements as before but in full-range and more challenging and functional tasks (e.g., hand behind back, hand to curl hair). Participants will be in sitting in a relaxed position for imaging movements. They will be instructed to watch the videos and then close their eyes and to imagine themselves performing the same movements in a smooth and pain-free manner as if it was real in all its aspects, including the timing taken to move. Participants will be advised not to imagine watching themselves performing the movement but to imagine actually performing the movement in the first person. They will execute two series of 20 repetitions for every imagined movement in each session. Additionally, participants will be asked at home to watch the videos twice and to practice for a total of 15 min each day.

The next stage (weeks 5–6) will involve isometric contraction of the rotator cuff and scapulo-thoracic muscles using dynamic glenohumeral and scapulo-thoracic neuromuscular control exercises. It is believed that the activation of these muscles will serve as an ideal bridge between imagined movements and actual shoulder movements used in the next stage using mirror therapy (because there would not be shoulder movement, thus minimizing the potential for sensorimotor incongruence) and that the activation of these muscles might sharpen the cortical representation of the shoulder [13]. During the first week (week 5), participants will receive instruction on dynamic glenohumeral neuromuscular control exercises aiming to contract the rotator cuff muscles [29] and scapulo-thoracic muscles [30] in isolation. They will perform neuromuscular control exercises for three sets of 10-s repetitions with a 2-min rest period between sets. During the second week of this stage (week 6), the progression will involve maintenance of the local muscle contraction while participants move their shoulder in a pain-free manner in different directions. Exercise dose will be the same as during week 5. Participants will be asked to practice at home these tasks for a total of 15 min each day.

The next 4-week stage (weeks 7–10) will involve the use of mirror therapy with different progressions. Participants will be seated in a comfortable chair, towards the edge of the chair seat allowing for movement, but also providing some trunk support. The proposed mirror therapy will be demonstrated and explained to the subjects by the physiotherapist. Next, a standing mirror on wheels will be placed in front of the participant with the reflective side facing the uninvolved side. The affected arm will be placed behind the mirror. The participant will be asked to lean forward slightly, allowing them to view the complete uninvolved arm in the mirror. Mirror exercises will begin with simply watching the reflection of the unaffected arm in the mirror and then progressed from static to active and functional movements. When possible, gentle and synchronous movements of the affected arm will be encouraged behind the mirror. Two series of 12–15 min will be performed in each session, with 2 min between series to allow for resting and relaxing the arm. Additionally, participants will be asked to practice this task at home for 15 min each day with a mirror provided by researchers conducting the study.

Participants will be encouraged to move slowly and easily, breathing comfortably and focusing on the movement of the uninvolved arm. The intervention will allow subjects to move the uninvolved arm giving the “illusion” that their involved arm is moving through the full active ROM. Participants will be advised to stop if they have an increase in pain either during or directly after mirror therapy.

A full description of the GMI training program is provided in Table 2.

**Table 2 Tab2:** Summary of progressions used for the Graded Motor Imagery (GMI) training program

Stage	GMI training
1 (weeks 0–2)	*Laterality recognition* Using Recognise software Determine whether left or right side of shoulder Progress by time for which image was presented
2 (weeks 2–4)	*Imagined movements* Using video of model performing movements Small-range movements during first week Full-range movements during second week
3 (weeks 4–6)	*Isometric local muscle recruitment* Rotator cuff muscles Scapular muscles Add pain-free movement to local contraction
4 (weeks 6–8)	*Mirror therapy* Keep the affected arm still in a comfortable position/keep the unaffected arm still in the same position and just observe the reflection Keep the affected arm still in a comfortable position/move the unaffected arm through its full-range of movement (ROM) in different directions
5 (weeks 8–10)	*Mirror therapy* Move the affected arm towards the limit of pain in the restricted/painful direction(s) of movement and keep that position/move the unaffected arm through its full ROM in the painful/limited directions Move the affected arm towards the limit of pain in the restricted/painful direction(s) of movement/copy with the unaffected arm through a full ROM (synchronous movements)

Should sustained symptom exacerbation occur in any of the stages, the appropiate parameters will be reviewed and possibly reduced.

### Standard medical and physical therapy care program

Participants randomized to standard medical and physical therapy care will receive a 10-session treatment program of the same duration as the CNS-focused treatment. This standard treatment will include one corticosteroid infiltration provided in the early acute stage followed by a multimodal physical therapy program including analgesic modalities (e.g., TENS, cryotherapy) and exercise and manual therapy techniques addressing the specific mobility deficits of each patient [31]. Physical therapists will be instructed not to include interventions that were similar to those used in the group receiving the CNS-focused protocol (e.g., using mirrors or imagined movements) and to include a home program that involves a training load comparable to that in the other group.

### Primary and secondary outcome measures and assessment points

The primary outcome measured is self-reported shoulder pain-related disability as measured on the Shoulder Pain And Disability Index (SPADI) questionnaire. The Spanish version of the SPADI has high internal consistency (Cronbach α: 0.916) and excellent test-retest reliability (ICC 0.91) [32]. Secondary outcomes are as follows:The Numeric Pain Rating Scale (NPRS), a valid and reliable measure of shoulder pain [33]Goniometric assessment of active shoulder ROM which is valid and reliable [34, 35]Two-point discrimination threshold measured at one standardize site on the affected shoulder (5 cm distal to the lateral border of the acromion) [36], following an established protocol [37]Laterality judgement accuracy using the NOI Recognize online program (www.noigroup.com) and following an established protocol [38]The Spanish version of the Tampa Scale of Kinesophobia, a valid and reliable measure of fear of movement [39]The Patient Specific Functional Scale, a reliable, valid and responsive instrument that can be used in patients with a primary shoulder complaint [40]

Assessment will occur at baseline, at the end of the treatment program (week 10), and at 3 and 6 months’ follow-up. At baseline, a clinical assessment of symptom distribution, history of the present and previous shoulder complaints, red flag screening, medical history and general health status will also be performed.

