In this first stage, only localization of the stimulus will be trained. Participants will be shown a digital standard photograph of the shoulder on which nine numbered grids will be marked. The spacing of the grids will be based on the current normative data pertaining to two-point discrimination of the affected joint (e.g., (45.9 mm ± 18.4 mm) [26]. For the shoulder localization blocks, the superior border will be set as 1 cm proximal to the acromioclavicular joint and the lower border reaching the deltoid insertion. While the participant views the photograph and nine-block grids, they will be taught via tactile stimulus with the back of the blunt end of a pencil, where each block is in relation to their shoulder, thus familiarizing them with the nine-block grid [13, 27]. After the familiarization period, the therapist, using a random number sequence, will press lightly on a particular point with the blunt end of a pencil for about 2 s. Pressure will be kept to a minimum to avoid pain provocation. Participants will be instructed to refer to the picture and to indicate which grid has been stimulated. With a correct identification of the area, the therapist will proceed to the next block for identification. If the participants make an error, they will be told which grid (number) has in fact been stimulated, and then the actual position of the grid that they have incorrectly indicated will be stimulated. This in essence will help the participant to develop a greater ability to identify the stimulated grid. Three blocks of 60 stimuli with an interstimulus interval of 15 s and a 3-min rest period between blocks will be used during the treatment session.

At the first session, participants will be accompanied by someone who can assist them to undertake training at home. This assistant will be trained in the task and participants will be advised to undertake 15 min of training at home in addition to the clinic session. Participants will be given a photograph of a standard shoulder on which the stimulation points will be marked and several sets of 60 random number sequences to use for training at home. If at the end of the second week (first stage), for participants who have less than 80% accuracy with one test block of 60 stimuli, the training will be extended for an additional week.

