### Significance and implications for practice

Preliminary data suggest that treatments that target CNS function are a promising approach to the treatment of people with shoulder pain including patients with FS. In the context of modest effects from most available physical therapy treatments for FS, this CNS-focused approach may lead to improved clinical outcomes. The trial should determine if the CNS-directed program is more effective than traditional interventions at reducing pain intensity and improving function in a FS cohort and will follow up participants for 6 months, providing important information on the persistence of any treatment effects. The inclusion of variables related to functional reorganization of the brain, such as the two-point discrimination threshold and laterality judgement accuracy, will also allow for the first time to explore responsiveness to change of these tests after treatment in a population with shoulder pain. In addition, this study provide a good oportunity to explore the relationship between shoulder pain, cortical changes and clinical markers in people with FS. Finally, the flexible structure of the interventions comprising the CNS-focused approach closely reflects the real-world clinical practice.

CNS-directed interventions constitute a completely new treatment paradigm for the management of shoulder pain and, in particular, people with FS. Feelings of stiffness in the back have been recently demonstrated to be a multisensory perceptual inference consistent with protection rather than reflecting biomechanical properties of the back [43]. Stiffness is a main characteristic in people with FS and the prevailing view is that it is related to a capsular fibrosis despite the cause being still unknown [44]. The positive effects in ROM observed in preliminary research conducted in people with FS after brief interventions targeting the CNS challenge the prevailing view that stiffness in FS is an isomorphic marker of the biomechanical characteristics of the shoulder. The results of this study should have the potential to address this issue and change the current physiotherapy management of FS.

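### Laterality accuracy is tested on the program that only the CNS arm trains on, so a group difference cannot separate practice from cortical change; two-point discrimination is affected more weakly

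*Protocol article*

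**What the plan says.** All of the following is in the protocol article.

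- **Laterality test.** The section on primary and secondary outcome measures lists "Laterality judgement accuracy using the NOI Recognize online program" among the secondary outcomes and refers to a cited protocol for how it is run.
- **Laterality training.** The section on Graded Motor Imagery (GMI) training says of the CNS arm: "An online computer program (Recognise Online, NOI Group, Adelaide, SA, Australia) will be used to present participants with a random selection of photographs". The task is to judge whether a left or a right shoulder is shown. For home: "Participants will be asked to practice this task at home for 15 min each day". The text and Table 2 both confine this stage to the first two weeks.
- **Two-point test.** It is taken at one site on the affected shoulder, "5 cm distal to the lateral border of the acromion".
- **Tactile training.** The section on graded sensory discrimination training places the localization grid so that "the superior border will be set as 1 cm proximal to the acromioclavicular joint and the lower border reaching the deltoid insertion". Grid spacing is derived from two-point discrimination norms. The trained tasks are localization, stimulus type and graphesthesia.
- **Comparator.** The section on the standard care program tells its therapists to avoid content resembling the CNS program.
- **Analysis and reading.** The Statistical analysis section compares the groups on all primary and secondary outcomes and sets significance at p < 0.05. The section on significance and implications for practice introduces the two measures as "The inclusion of variables related to functional reorganization of the brain, such as the two-point discrimination threshold and laterality judgement accuracy". It plans to explore their responsiveness and how pain, cortical change and clinical markers relate.

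**The concern.** An outcome that one arm rehearses and the other is kept away from can differ between arms because of the rehearsal alone. Laterality accuracy is in that position: task and program are the same in training and testing, and only one arm trains. Two-point discrimination is nearby: one arm receives weeks of tactile training with error feedback over what is probably the same skin.

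Both measures stand in the list of secondary outcomes beside pain, movement and function, and both will get a between-group test. They are also the only variables the article names as reflecting brain change. The risk is in interpretation. A difference on either could be reported as a secondary benefit, or as support for the proposed mechanism, when the design leaves task learning as an equally available explanation. Exploring responsiveness meets the same difficulty when one arm has practised the test.

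**Working it through.** The article gives no figure for a practice effect, so there is no bias estimate to reproduce. The check compares training with testing, measures the exposure and looks at the timing.

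**1. Training against testing**

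| | Laterality accuracy | Two-point discrimination |
|---|---|---|
| Instrument | Same vendor's online program in both | Different tasks: the two-point test is not trained |
| Task | Same left/right shoulder judgement | Localization, stimulus type and graphesthesia trained |
| Location | Not applicable | Test site probably inside the trained grid |
| Comparator exposure | None planned | None planned |
| Route to a spurious difference | Direct practice | Transfer from related tasks |

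That the two-point site lies inside the grid is an assumption. It requires the deltoid insertion to be more than 5 cm below the acromion, and the article does not give that distance. The grid borders are stated for the localization work; for graphesthesia, from week 4, the article says only that letters are drawn on the shoulder.

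**2. Exposure in the CNS arm**

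Inputs: 15 min of home practice per task; five home sessions a week (CNS-focused treatment program section) or daily (GMI section); 5 s per photograph at the start; three blocks of 60 tactile stimuli at 15 s with 3-min rests; 10 sessions of 60 min.

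- Laterality, home: 15 × 5 × 2 = 150 min; if daily, 15 × 7 × 2 = 210 min.
- Photographs per home session at 5 s without rests: 15 × 60 / 5 = 180. Over two weeks: 180 × 10 = 1,800, or 180 × 14 = 2,520. These are rough: rests lower them, and the planned shortening of presentation time raises them.
- Tactile, home: 15 × 5 × 10 = 750 min.
- Tactile, clinic: 3 × 60 = 180 stimuli per session; 180 × 15 / 60 + 2 × 3 = 51 min.
- Tactile total if every session held the full dose: 750 + 10 × 51 = 1,260 min. This is a ceiling. In weeks 7–10 mirror therapy takes 2 × 12 + 2 = 26 to 2 × 15 + 2 = 32 min, so both together would need 77 to 83 min of a 60-min session.

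Planned exposure in the comparator is 0 for both. These figures measure exposure, not bias.

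**3. Timing**

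Laterality training ends at week 2 and the first post-treatment assessment is at week 10, a gap of 10 − 2 = 8 weeks. Tactile training runs to week 10, so there is no gap before the two-point test.

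**4. Is a significant difference automatic?**

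The plan's SPADI calculation reproduces: 17 / 16 = 1.0625 SD, and a two-sided t-test at 0.05 with 80% power needs 14.93, so 15 per group (power 80.2%). Applied to two-point discrimination, assuming the normative SD of 18.4 mm that the article quotes, 1.0625 × 18.4 = 19.55 mm, which is 19.55 / 45.9 = 43% of the quoted norm. This is a simple two-group comparison of means, not the planned repeated-measures analysis, but it shows that significance is not assured.

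**The case against.** The strongest reply has four parts.

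- **Measuring what the treatment targets is ordinary design.** The therapy is meant to work by training these abilities, so improvement after training is the expected first step. That is right, and it is why the measures should stay. It supports calling them uptake measures; it does not make a difference evidence of cortical change.
- **The article's wording is restrained.** It calls the variables related to reorganisation and speaks of exploring. Its statement of what the trial should determine covers pain intensity and function only. This stands. A reader might infer that the protocol treats a difference as proof of reorganisation; it does not say so.
- **The effect may be small.** Laterality training stops 8 weeks before the first post-treatment test, and no practice effect is quantified. A reader might infer that a significant difference is almost built in. The documents do not support that, and the detectable difference worked out above points the other way.
- **The test images may already differ from the training images.** The laterality test follows a cited protocol that is not at hand. If it does use separate images, the fix only needs to say so. Separate images remove familiarity with particular photographs, but not practice at the task.

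Two further inferences go too far. One is that two-point discrimination is itself trained; no two-point task appears among the five stages. The other is that a difference would show practice and not reorganisation; the design cannot tell them apart in either direction.

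**Conclusion.** The concern holds as a limit on interpretation. For laterality, identity of task and program together with one-sided training means that a between-group difference cannot distinguish practice from cortical change. For two-point discrimination the same limit applies more weakly, by transfer of learning, and depends on the anatomical assumption above. The size of any practice effect is unknown, and for laterality it may have partly faded by week 10. SPADI, its sample size and the other secondary outcomes are untouched. The point is worth correcting because outcome status, instrument and test site are all fixed in this article, and the correction is cheap.

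**What to change.** - In the sections on outcome measures and on significance and implications for practice, designate both measures as target-engagement (training-uptake) measures instead of secondary efficacy outcomes. Carry this into the Abstract and the Statistical analysis section so that the lists agree.
- State that a between-group difference on either will not by itself be read as brain reorganisation or as efficacy.
- Score laterality at all assessments, baseline included, on an image set not used in training; if the cited test protocol already ensures this, say so.
- Keep the planned links with pain and clinical markers exploratory.

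The cost is wording, one reserved image set, and the loss of efficacy status for two measures. No change to the sample size or the SPADI analysis is needed.

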### Recruitment procedures

Participants will be recruited from different outpatient private clinics and rehabilitation services of different hospitals of the region of Valencia (Spain). In addition, posters will be distributed in the community and advertisements in social media will be placed to increase the potential number of participants in the study. Physical therapists and primary care practitioners will be contacted and invited to recruit participants after providing them with brief information about the study. Involved practitioners will identifiy potentially suitable patients and, after providing them with information about the study, will invite them to contact the research team. Upon contact by potential participants, a researcher will explain the study and assess them for study eligilibily via telephone. If the potential participant remains interested in participating in the study, they will be invited to a baseline session. During that session, one researcher will provide to the patient an information leaflet, confirm eligibility, and obtain a signed consent form. Baseline outcome data will be collected during this session, following which the participant will be randomized.

Adherence to treatment will be enhanced by careful explanation of the time demands of participation and regular contact by a researcher who will send repeated reminders to participants by email and make telephone calls to ensure adherence to the time schedule including follow-up sessions.

The schedule of the enrollment, interventions and assessments is shown in Fig. 1.

